### Adherence and dropout

At the start of each stimulation session, the patient will confirm their willingness to participate. The patient will indicate their interest in taking part in our study before each stimulation session, and they will be free to leave at any moment. During the patient’s participation in the study, the research clinician will ensure that the patient is still eligible to participate. An individual will be removed from the study upon losing eligibility or reporting any major negative side effects.

Thus, patients will be asked to drop out of the investigation if any adverse effect occurs after stimulation or if they fail to cooperate to the extent that the normal protocol of the study cannot be carried out. Patients will be free to drop out at any point if they so desire. To improve adherence to the study procedures, telephone follow-up will be carried out during the washout phase so that any adverse consequences can be properly managed. Moreover, if any brain abnormalities are observed during the MRI (e.g., white matter hyperintensities, cerebral vascular lesions, or evidence of space-occupying lesions) or EEG assessments (e.g., epileptiform activity, ictal patterns) or after blood testing (e.g., exaggerated levels of sNfL), the patient will be referred to the proper medical services for further analysis and consideration, which will inform the decision of whether the patient may continue in the study.

Although rescue treatment will not initially be required, nonresponders will have the option to receive another 5 sessions of real iTMS bilaterally over M1 at the end of the study as an add-on rescue treatment. Patients and their relatives will be instructed to maintain their normal daily routines and not to alter their physical exercise patterns, diet, sleep schedules, or any other nonpharmacological treatment throughout the study, as well as to report any change.

Dopaminergic medication for all patients will be stabilized for at least 2 months prior to the study. Patients will need to maintain their dosage of dopaminergic medication until the completion of Phase II. In addition, assessment of nondopaminergic medications will be conducted to determine their influence on the tests performed.

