### Safety assessment

Although existing research on the use of iTBS to treat PD patients has not identified any significant side effects, patients will be carefully monitored for the recognized possible concerns, such as epilepsy. Each treatment and follow-up session, therefore, will include a safety assessment. Other potential reactions, such as fatigue, dizziness, and headache, will be recorded to evaluate the safety of iTBS for PD patients. The most frequent side effects of the EEG recordings are expected to be headache and pain or discomfort in the scalp. Pain and hematoma at the blood sampling site, as well as a vasovagal reaction, syncope, or fainting, may be the most frequent side effects after blood collection. Following each real or sham iTBS phase, safety questionnaires will be administered to the patients, and the results will be recorded and analyzed according to severity, seriousness, and causality. Patients’ vitality, physical health, and mental health will also be monitored to assess any potentially major ill effects.

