**Figure 2 fig2:**
[figure not shown]
Timeline of study-related events during Phase I/II. After randomization, patients will undergo baseline evaluations. This first examination will include clinical, cognitive and neuropsychiatric evaluations; structural and functional resting-state neuroimaging; EMG; EEG; and blood sample collection. These tests will be performed over a maximum of 1 month and prior to the first iTBS session, with the exception of EMG recording (which will be carried out on the same day, immediately before this first session). Once baseline evaluations are completed, patients will undergo iTBS intervention: one daily (real or sham) iTBS session over the bilateral M1 at 80% of the aMT for five consecutive days. Subsequently, the post-iTBS evaluation stage will start with TMS-EMG data acquisition and clinical examination. The rest of the tests will be performed in the following 4 weeks after the last TMS session (week 1: EEG, clinical evaluation, serology and neuroimaging; week 2: cognitive and neuropsychiatric evaluations, clinical evaluation; week 4: last clinical exploration). The same timeline will be followed for Phases I and II.

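### The withdrawal rules conflict (major side effects only, or any adverse effect), and both take the patient out of the study and not just off stimulation

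*Protocol article*

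**What the plan says.** Adherence and dropout (protocol article) gives two thresholds in consecutive paragraphs. The first reads: "An individual will be removed from the study upon losing eligibility or reporting any major negative side effects". The next, introduced as a consequence of the first, reads: "patients will be asked to drop out of the investigation if any adverse effect occurs after stimulation". In both, the patient leaves the study. Neither describes stopping stimulation while staying in follow-up.

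Safety assessment treats minor reactions as something to observe: "Other potential reactions, such as fatigue, dizziness, and headache, will be recorded to evaluate the safety of iTBS for PD patients". For the safety questionnaires given after each phase it adds that "the results will be recorded and analyzed according to severity, seriousness, and causality".

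Adherence and dropout also has a route based on test findings. If MRI or EEG shows an abnormality, or "after blood testing (e.g., exaggerated levels of sNfL), the patient will be referred to the proper medical services", the result of the referral is something "which will inform the decision of whether the patient may continue in the study". Table 1 lists serum NfL as an exploratory outcome. The Figure 2 legend places these tests after allocation: "After randomization, patients will undergo baseline evaluations".

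Statistical analysis says that patients with missing outcome data are at first removed from each data subset, and that other strategies, with last observation carried forward as the example, will also be used. Recruitment and sample size requires at least 21 patients and plans for 24.

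**The concern.** A patient with a mild headache after a session stays in under one sentence and is asked to leave under the next. Staff applying the protocol cannot tell which governs, and different patients may be handled differently. If the wider rule is applied as written, the severity grading planned for safety has no bearing on who remains.

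What is at stake is the randomised comparison. In a two-period crossover, a patient who leaves in Phase I never supplies the other condition, so the within-patient contrast is lost for the primary MDS-UPDRS outcome as well as for the exploratory ones. With complete-case removal as the first step, an adverse effect then becomes exclusion from the analysis. Safety data from the second phase would also come only from patients who had no adverse effect in the first.

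**Working it through.** **1. The texts side by side.**

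| Place | Trigger | Consequence |
|---|---|---|
| Adherence and dropout, first paragraph | lost eligibility or a major side effect | removed from the study |
| Adherence and dropout, second paragraph | any adverse effect after stimulation | asked to leave the investigation |
| Safety assessment | fatigue, dizziness, headache and similar | recorded, then analysed by severity, seriousness and causality |

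Rows 1 and 2 give opposite answers for every adverse effect that is not major. Row 3 expects such effects to occur and be graded, which is hard to combine with row 2.

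**2. Margin.** Inputs from Recruitment and sample size: 21 needed, 24 planned. 24 − 21 = 3 patients can be lost, and 3/24 = 12.5%.

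**3. Withdrawal rate that uses up the margin.** The article gives no adverse-effect rates, so every rate below is an assumption. Let r and s be the chance of withdrawal in a real and a sham phase, with 12 patients per sequence.

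- Expected completers = 24(1 − r)(1 − s).
- With r = s, 24(1 − r)² = 21 gives r = 1 − √0.875 = 0.065. Check: 24 × 0.935² = 21.0.

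About 6.5% per five-session phase is therefore enough, with no difference between real and sham.

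**4. Range, and when the loss becomes selective.**

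- Real phases retained = 12(1 − r) + 12(1 − s)(1 − r).
- Sham phases retained = 12(1 − s) + 12(1 − r)(1 − s).
- Power uses the noncentral t with n − 2 degrees of freedom and n set to the expected completers. The standardised within-patient effect is back-solved from 21 patients at 80% power and two-sided 0.05, which gives 0.645.

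| r (real) | s (sham) | Completers | Real phases | Sham phases | Power |
|---|---|---|---|---|---|
| 5% | 5% | 21.7 | 22.2 | 22.2 | 81% |
| 20% | 5% | 18.2 | 18.7 | 20.5 | 74% |
| 20% | 20% | 15.4 | 17.3 | 17.3 | 65% |
| 40% | 10% | 13.0 | 13.7 | 17.3 | 56% |

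Example, second row: 24 × 0.80 × 0.95 = 18.2; real 12 × 0.80 + 12 × 0.95 × 0.80 = 18.7; sham 12 × 0.95 + 12 × 0.80 × 0.95 = 20.5.

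Equal rates give equal retention of real and sham phases. Imbalance appears only when r and s differ. Completers can fall below 21 in either case.

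**5. The test-findings route.** The listed MRI and EEG triggers are clinical findings such as vascular lesions or epileptiform activity. They are not the Table 1 outcomes of grey-matter volume, cortical thickness, spectral power and connectivity. Only serum NfL is both a trigger and a listed outcome. It is exploratory, the article gives no cut-off, and the route runs through referral and an individual decision.

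**The case against.** A reader might infer that real-phase data would be lost selectively. The article does not support that. It reports no adverse-effect rates, says existing research found no significant side effects, and describes a sham coil with similar sound and sensation. Unequal rates are plausible because the sham coil delivers no stimulation, but that is an assumption. Moreover, a patient withdrawn in a first real phase takes the sham data away too, so under complete-case removal the whole patient is lost.

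A reader might also infer that patients are removed on their results. That too goes beyond the text: removal after a test finding is not automatic, the primary outcome is not a trigger, and the article does not say which eligibility criteria can be lost. Removal on a baseline MRI or EEG finding precedes any stimulation and cannot be caused by it.

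The Statistical analysis section does not stop at complete cases, and it says that bias from missing data will be considered. This is fair. But the one method it names, last observation carried forward, cannot supply a phase that never took place; a value carried over from Phase I was measured under the other condition.

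Finally, the plan already assumes about 20% drop-out. Yet 24 × 0.80 = 19.2, below 21, so the margin actually available is 12.5%. That is a separate sample-size matter and is used here only to show how little room there is.

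None of these arguments removes the contradiction or the absence of any distinction between stopping stimulation and leaving the study.

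**Conclusion.** The contradiction is certain and rests on the text alone. The wider rule also conflicts with the Safety assessment section. Because either rule ends study participation and the first analysis step is complete-case, the wider rule applied literally could cause treatment-related loss of randomised patients.

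The size depends on rates that the article does not give. Under equal rates, about 6.5% per phase uses up the whole margin of 3 patients. Over the assumed range shown, expected completers run from 21.7 down to 13.0 and power from 81% down to 56%. These figures assume that every adverse effect leads to withdrawal and that the implied effect size is correct. Selective loss is a possibility that depends on unequal rates and is not a conclusion. The NfL route is a smaller, secondary point.

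**What to change.** - Reconcile the two sentences in Adherence and dropout with each other and with Safety assessment. Which threshold applies is for the sponsor to decide.
- State that stopping stimulation is not leaving the study. Patients who stop are asked, subject to consent, to keep the outcome visits already scheduled, and their available data stay in the analysis as allocated.
- State that no patient is excluded from the analysis because of a serum NfL value measured after randomisation.
- For patients not yet enrolled, consider opening the envelope only after the baseline assessments and eligibility review. The Blinding section now opens it after consent, and baseline can take up to 30 days, so an allocation may be spent on someone who is never treated. Study protocol status reports thirteen patients already enrolled, so the change of procedure would have to be reported.

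The cost is protocol wording, a few outcome visits that are already planned and, if the envelope step moves, two allocation procedures within one trial of 24. Because four patients have already crossed over, the change is worth making promptly: visits missed after a withdrawal cannot be recovered later.

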## Discussion

PD is a progressive disorder caused by dopamine depletion, which contributes to the manifestation of characteristic related clinical symptomatology. Improving motor and non-motor functional outcomes is therefore a priority in the management of PD patients. Although a wide range of treatments is available, PD symptoms may progress, leading to severe impairment. The pharmacotherapy of PD relies on dopamine level restoration, and although good management of symptomatology is commonly achieved, this balance is maintained for only a short period of time, as complications related to medication may occur, thus impacting tolerability and treatment efficacy (Jankovic, 2002; Tambasco et al., 2018). Numerous therapeutic alternatives have been developed to ameliorate the symptom impact and disability associated with the disease and its first-line pharmacology options (Mishima et al., 2021; Serva et al., 2022). In fact, different rTMS modalities are considered a potential therapy for PD, given the safety and lack of side effects after application (Wagle Shukla et al., 2016). Nevertheless, although a variety of rTMS protocols have been demonstrated to be effective, many of them have limited benefits in terms of time and effects (Chou et al., 2015; Zanjani et al., 2015); thus, an increasing number of studies has examined the therapeutic impact of TBS, which has a shorter stimulation duration and more intense stimulation sequence, on motor and nonmotor symptoms in PD patients (Cheng et al., 2022). However, inconsistent conclusions have been reported because only a few TBS studies have been performed; hence, the magnitude and persistence of the TBS effect remain debatable.

Most previous studies have supported the clinical efficacy of cTBS over the SMA for improving motor function in individuals with PD in the OFF medication state, but the clinical effect and ultimate clinical importance of iTBS over the M1 remain unclear and controversial. Thus, while a single session of cTBS over the M1 did not have any motor or clinical effects in PD patients in the OFF medication state (Eggers et al., 2010), a study using a single session of iTBS over the M1 was promising for alleviating complications in PD patients in the ON medication state (Degardin et al., 2012). However, some disagreements regarding the application of excitatory or inhibitory TBS protocols and the recommended brain targets during the ON medication state still need to be clarified (Cheng et al., 2022).

There is broad consensus that TBS protocols, like other types of rTMS, may promote cortical plasticity that treats disease, improves health, and modifies brain activity. Moreover, evidence indicates that the after-effects of TBS protocols are due to underlying mechanisms of synaptic plasticity. Accordingly, LTP and LTD are thought to be the processes underlying the stimulation and suppression of MEPs by iTBS and cTBS protocols, respectively. In this regard, the restoration of post-TBS MEP amplitudes to their baseline levels is a neurophysiologic indicator of the clinical effectiveness and efficacy of the mechanisms underlying cortical plasticity (Oberman, 2010; Pascual-Leone et al., 2011).

However, it is important to note that LTP and LTD pertain to extremely specific neurophysiologic events at the level of individual synaptic connections, and the alterations induced by TBS are not always limited to specific individual synaptic terminals. It is more probable that many of the positive effects of TBS are the result of the secondary activation of glial cells, although there is limited information regarding the response of glial cells to these neuromodulation techniques (Cullen and Young, 2016), particularly in relation to iTBS-induced plasticity effects (Cacace et al., 2017). Moreover, knowledge about how intracortical structures, cortico-subcortical functional connectivity, and brain volume changes are involved in the modulatory effects of rTMS and TBS is still limited (Di Lazzaro and Rothwell, 2014; Peters et al., 2020; Jannati et al., 2023; Kirkovski et al., 2023).

Although the postulated mechanism of iTBS (i.e., stimulating neuronal and glial activity) has been demonstrated to prompt LTP-like plasticity *in vivo* (Funamizu et al., 2005; Cullen and Young, 2016; Cacace et al., 2017), human studies targeting microglia and astrocyte reactivity in areas affected by neurological or psychiatric diseases are scarce. Thus, it has been hypothesized that the benefits of iTBS for reducing motor and nonmotor symptomatology in patients with PD, as well as many other brain-related diseases, might be due to effects on microglia and astrocytes, which play a protective role in neurodegenerative and neuroinflammatory diseases (Stanojevic et al., 2022). In line with the quantification of blood biomarkers of neurodegeneration, some recent studies have reported that excitatory frontal and parietal rTMS, in addition to improving cognition, is not associated with neuroaxonal damage or neurodegeneration in healthy populations according to plasma NfL concentrations (Redondo-Camós et al., 2022); thus, the effects of iTBS on reducing neurodegenerative pathology in animal models and humans still need to be tested. Furthermore, evidence from animal models and neurological patients suggests that TBS and rTMS protocols may induce changes in the regulation of BDNF expression (Zhang et al., 2007; Stevanovic et al., 2019) or changes in BDNF protein levels (Müller, 2000) and promote neuroprotection and neuroplasticity (Feng et al., 2012; Castillo-Padilla and Funke, 2016; Zuo et al., 2020). However, the role of BDNF in the effects of TBS on PD patients is still debated, as it may have a variable response to iTBS compared to cTBS, likely because the PD brain might be less susceptible to iTBS-induced motor plasticity and potentiation (Cheeran et al., 2008). Further investigation of BDNF down/upregulation is essential to better understand the scope and capacity of iTBS-induced plasticity.

While it has been demonstrated that a few sessions of rTMS or TBS can increase GM volume at the stimulation site as well as in more distal brain regions (May et al., 2007), the potential role of cerebral CT as a possible biomarker of iTBS treatment response in PD patients still needs to be assessed. These GM volume changes could demonstrate the substantial neuroprotective effects of rTMS or TBS, likely dependent on a wide range of micro- and macroscopic neural mechanisms (Ji et al., 2021; Jung and Lambon Ralph, 2021). In light of this, metabolic neuroimaging studies have provided additional evidence of neuroplastic changes after rTMS or TBS, as M1 rTMS was shown to influence the resting-state activity of the motor system after the stimulation had ended as well as in brain regions connected to the stimulation site (Lee et al., 2003; Rounis et al., 2005), demonstrating an acute reorganization of activity to other areas. Moreover, studies in PD patients have reported changes in functional connectivity between the M1 and basal ganglia or between the prefrontal areas and the SMA after low-frequency (Wang et al., 2023) or high-frequency rTMS (González-García et al., 2011), respectively. Despite the evidence demonstrating altered brain functional connectivity in PD, conclusive data regarding the potential link between clinical improvement and changes in the brain’s structural and functional connectivity after iTBS in these patients are lacking.

In conclusion, this study is designed to provide new insights that promise to advance our understanding of the efficacy of M1-iTBS in improving symptomatology in the early and middle stages of PD. We hypothesize that bilateral M1-iTBS will considerably improve motor functioning in PD patients, as measured by MDS-UPDRS parts II, III, and IV, in addition to alleviating nonmotor symptoms. A growing body of evidence from preclinical and human studies allows us to further hypothesize that the striatal endogenous dopamine release triggered by iTBS may rebalance cortical excitability and restore compensatory striatal volume changes, increasing the functional connectivity of striato-cortico-cerebellar networks while also positively impacting neuroglia and neuroplasticity modification.

Thus, by identifying potential electrophysiological, neuroimaging and serum markers underpinning iTBS-induced dopamine-dependent corticostriatal plasticity, our study could pinpoint the ideal biomarkers responsible for short- and long-lasting effects on motor function in PD, offering these patients an optimized adjunct to dopamine replacement therapies.

### Study protocol status

This study is currently ongoing and started recruitment in June 2022. The first thirteen patients have been enrolled, and four of them have already undergone the crossover intervention. The estimated completion date is December 2023.

## Summary and conclusions

This randomized double-blind sham-controlled crossover protocol study will investigate the neural and behavioral effects of iTBS over the bilateral M1 on idiopathic PD. The present combination of iTBS, cortical excitability measures, structural and functional neuroimaging data, and serum biomarkers represents a powerful approach that enables noninvasive, *in vivo* assessment and modulation of brain excitability, connectivity, and neuroprotection and neuroplasticity across motor and nonmotor brain networks in PD patients. We hypothesize that bilaterally stimulation of the M1 with excitatory iTBS will yield beneficial clinical effects that improve MDS-UPDRS-III scores in the ON medication state (i.e., motor improvement in PD patients) by modulating regionally specific changes in BG-cortical volume as well as by functional connectivity among the BG, cerebellum and cortical regions involved in motor processing. Moreover, we hypothesize that these functional and structural brain changes will be dynamically associated with the neuroprotective and neuroplasticity effects of real M1 iTBS reflected by stabilization of NfL and GFAP levels and by elevation of BDNF levels. Thus, these results may provide supportive evidence that the bilateral M1 is an optimal excitatory stimulation target for treatment among stable PD patients.

## Ethics statement

The study and the current protocol have been approved by the Andalusian Biomedical Research Ethics Committee (Ref.: 2169-N-19) in accordance with the Code of Ethics of the World Medical Association (Declaration of Helsinki) for experiments involving humans (World Medical Association, 2013). Furthermore, our study aligns with Spanish legislation on the grounds of biomedical investigation (Law 14/2007, July 03), personal data protection (Law 15/1999, December 13) and bioethics. Every participant will provide voluntary written informed consent before participating in our study. The findings will be distributed through (open-access) peer-reviewed publications, networks of scientists and professionals, the general public, patient associations, and presentations at conferences.
